### Sample size

Sample size and power were estimated with PASS software [27]. The trial's primary outcome is the proportion of unplanned hospital readmissions among patients discharged from a GIM team. We assume an intracluster correlation coefficient of 0.01. In this trial we expect there will be in excess of 200 patients admitted into each clinical teaching team in the 2-month intervention period. In total there will about 4000 patients admitted into and discharged from twenty clusters (teams) over five hospital sites. We assume that a typical rate of readmission among GIM patients within 30 days after discharge is ten percent. When significance is set at p < 0.05, the trial would have 93% power to detect a 5.0 percentage-point lower rate of unplanned hospital readmission among patients discharged from intervention CTTs than control CTTs (i.e., 10% versus 5%). A 5.0 percentage-point difference would represent a fifty-percent difference in readmission rates between intervention and control team patients.

If the rate of readmission within 30 days of discharge from GIM treatment is five percent, and if the intracluster correlation coefficient is 0.01, then the trial has 67% power to detect a 2.5 percentage-point lower rate of readmission among patients discharged from intervention teams. Again, this is a fifty-percent difference (i.e., 5% versus 2.5%).

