The readmission dataset will be constructed with criteria similar to van Walraven et al. [20]. Patients will be identified as eligible for the readmission pool if they had a nonelective admission to one of the participating sites' GIM divisions through its medical or surgical department, were discharged alive from the participating site's GIM division in the same index admission, and had a nonelective medical or surgical readmission to any Ontario hospital within either 7 days or 30 days of discharge of the index admission. Patients will be excluded if they were admitted from or discharged to another hospital in the index admission; if they had no patient identifier or an invalid identifier; if they lacked key information; or if they exceeded the 99^th ^percentile of distributions of the following variables for all Ontario hospitals: hospital length of stay, number of previous hospitalizations, number of follow-up visits, or case resource consumption.

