#### Readmission

Two patient follow-up periods will be investigated for unplanned hospital readmission: the primary outcome, 30 days post-discharge, and a secondary outcome period of seven days post-discharge. Discharge records will be examined for patients discharged to home between one week after intervention period commencement and one month after intervention conclusion. Readmission proportions will be calculated for patients discharged from intervention and control group teams. The significance of the difference in proportions will be tested with chi-square and association statistics adjusted for the cluster randomized design [29-32]. The primary aim of the trial is to estimate the population-level intervention effect on binary-coded readmission outcomes; consequently, generalized estimating equations will be employed to control for clustering.

Some patients could have multiple hospital admissions, possibly to different hospitals during the study period. Furthermore, some of the admissions may qualify as an "outcome" while others do not. This situation raises a possibility that patients could change clusters (teams) during the trial, by being readmitted to a different GIM team within the same hospital that discharged them earlier in the intervention period. Therefore, a patient will contribute an observation to the analysis only from their first admission during the intervention period. If the readmission is to a different hospital than the index admission, then the readmission is 'credited' to the hospital of the index admission.

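### The 93% and 67% power figures need about 200 analysed patients in each of 20 equal teams and a normal reference; the cohort rules and the 20 teams get no allowance

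*Protocol article*

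**What the plan says.** The Sample size section assumes an ICC of 0.01 and more than 200 admissions per team over the two-month intervention period. It then totals them: "In total there will about 4000 patients admitted into and discharged from twenty clusters (teams) over five hospital sites". The main control rate is set as follows: "We assume that a typical rate of readmission among GIM patients within 30 days after discharge is ten percent". On that basis "the trial would have 93% power to detect a 5.0 percentage-point lower rate of unplanned hospital readmission" (10% v 5%). For a control rate of 5%, "then the trial has 67% power to detect a 2.5 percentage-point lower rate of readmission among patients discharged from intervention teams".

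The analysed cohort is defined elsewhere in the article.

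- **Outcomes: measurement, Readmission data.** The index admission must be nonelective and the patient discharged alive. "Patients will be excluded if they were admitted from or discharged to another hospital in the index admission". Patients without a valid identifier or with key information missing are also dropped, as are those above the 99th percentile on any of four variables.
- **Statistical methods, Readmission.** Only patients discharged home are examined, from one week after the intervention starts to one month after it ends. In addition, "a patient will contribute an observation to the analysis only from their first admission during the intervention period".

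The Randomization section gives five strata (hospitals) of four teams, two per arm in each, so 10 teams per arm. The primary analysis is by generalized estimating equations. The article names no reference distribution.

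**The concern.** The power count is of patients admitted and discharged. The analysis count is what remains after the cohort rules. Deaths, discharges to places other than home, elective admissions, repeat admissions, transfers, incomplete records and outliers may all sit inside the 200 but outside the analysis. The Sample size section holds nothing back for them.

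Two further simplifications act in the same direction. The teams are treated as equal in size, and the figures match a normal reference although only 20 randomised units carry the treatment comparison.

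At stake is how a null result would be read. The 5% v 2.5% scenario starts from only 67%, so a few points there matter more than in the main scenario.

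**Working it through.** **Inputs.** From the Sample size section: ICC 0.01, 200 per team, alpha 0.05 (sidedness not stated), rates 10% v 5% and 5% v 2.5%. From Randomization: 10 teams per arm, 5 strata. Analysable patients per team (m) and the coefficient of variation of team size (CV) are not in the article; values used for them below are assumptions.

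**Formulas.**
- Design effect: DE = 1 + ((1 + CV²)m − 1) × 0.01
- Effective size per arm: n = 10m/DE
- SE = √[(p₁q₁ + p₂q₂)/n], δ = (p₁ − p₂)/SE
- Power: two-sided normal, or noncentral t with 18 df (20 teams − 2) or 14 df (20 − 5 strata − 1)

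**Step 1: the plan's own figures.** With m = 200 and CV = 0, DE = 1 + 199 × 0.01 = 2.99 and n = 2000/2.99 = 668.9.
- 10% v 5%: SE = √[(0.09 + 0.0475)/668.9] = 0.01434, δ = 3.487, power 93.7%.
- 5% v 2.5%: SE = √[(0.0475 + 0.024375)/668.9] = 0.01037, δ = 2.412, power 67.4%.

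Pooling the null variance gives 93.6% and 67.3%. Both versions agree with 93% and 67% to within a point. Other conventions do not match both figures: one-sided normal gives 96.7% and 77.7%, and a continuity correction gives 92.1% and 61.9%.

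**Step 2: t reference, nobody lost.** The same δ gives 90.9% and 62.6% on 18 df, or 90.0% and 61.2% on 14 df. This step uses only the article's own numbers.

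**Step 3: fewer analysable patients (assumed), equal teams.**

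| m | DE | normal (unpooled) | t, 18 df |
|---|---|---|---|
| 180 | 2.79 | 92.9%, 65.9% | 89.9%, 61.1% |
| 160 | 2.59 | 91.8%, 64.0% | 88.6%, 59.2% |
| 140 | 2.39 | 90.4%, 61.7% | 87.0%, 57.0% |

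Under t with 18 df, the 10% v 5% scenario stays at or above 80% down to about 93 analysed patients per team.

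**Step 4: unequal teams (assumed CV 0.4), m = 140.** DE = 1 + (1.16 × 140 − 1) × 0.01 = 2.614 and n = 1400/2.614 = 535.6. With t on 18 df, power is 83.9% and 53.3%.

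**Step 5: the offset from the discharge window.** Take an eight-week intervention and 4.35 weeks to a month. The window is then (8 − 1) + 4.35 = 11.35 weeks. If every discharge in it counted, pro rata m = 200 × 11.35/8 ≈ 284 before exclusions. With none excluded, t on 18 df gives 93.4% and 67.1%. With 10% excluded (255 per team) it gives 92.8% and 65.8%; with 30% excluded (199 per team), 90.9% and 62.5%.

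**The case against.** The strongest reply has four parts.

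1. **The figures follow from their inputs.** This stands. A reader might infer that 93% and 67% were miscalculated; Step 1 shows they were not. The issue is what the inputs leave out.

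2. **The article does not show that fewer than 200 per team will be analysed.** This stands as well. No loss rate is given, the 200 is stated as a lower bound, and the window extends a month past the intervention. If all discharges in that window count, about 30% can be excluded and roughly 200 per team remain, which restores the stated figures under a normal reference. Against this, the first-admission rule refers to the intervention period. If it limits index admissions to that period, the longer window adds no patients beyond those behind the 200. The two rules leave the cohort ambiguous. Even the full gain, with nobody excluded, only just returns the stated figures under t with 18 df.

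3. **Fourteen degrees of freedom charge for the strata without crediting them.** This is fair. If modelling hospital absorbed part of the between-team variance (assumption: residual ICC 0.007), t on 14 df with 170 per team would give 93.8% and 67.8%, and with 140 per team 91.6% and 63.7%. The Sample size section claims no such gain, and the article gives no residual ICC. The main results here therefore use 18 df.

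4. **Reference distributions and size-variation terms are often left to a fuller document.** This is fair for the analysis method. It does not explain why the published power counts patients whom the article's own rules would exclude.

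**Conclusion.** The point holds in a limited form. The stated power needs about 200 analysed patients in every team and a normal reference, and the article makes no allowance for its cohort rules, unequal teams or the small number of clusters.

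The part that needs no outside assumption about numbers of patients is the t reference: about 91% and 63% on 18 df, or 90% and 61% on 14 df. If 140 to 180 per team are analysable, the figures are about 87–90% and 57–61%. With 140 per team and a CV of 0.4 they are about 84% and 53%. These last two sets rest on assumed values for the analysable number and the CV, keep the ICC at 0.01, and take no gain from stratification.

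A reader might go further and infer that the trial is underpowered for its main scenario, or that the lower figures are its true power. The article supports neither. The 10% v 5% scenario stays above 80% throughout the range shown, and the losses behind the lower figures are not documented. The 5% v 2.5% scenario is affected more, but the article already reports it openly at 67%.

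The normal reference is inferred from the reproduction, not stated. A generalized estimating equations analysis that kept a normal reference with 20 clusters would mainly threaten the type I error; the power loss appears once a t reference is used.

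**What to change.** 1. Reconcile the discharge window with the first-admission rule in the Readmission paragraph of Statistical methods, so that it is clear which index admissions count and over what period.
2. Estimate the analysable patients per team by applying the resulting cohort rules to past discharge records from the participating hospitals, and take the CV of team size from the same source.
3. Restate both power figures with that number, that CV and a small-sample t reference on the team-level degrees of freedom. Say whether hospital is modelled and, if so, what ICC remains. Show a range where inputs are uncertain, and label assumed values as such.

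The cost is a short recalculation and, most likely, two somewhat less favourable figures. Enrolment and the number of teams do not change.

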### Randomization

#### Sequence generation

The trial is a cluster randomized trial. Stratification is by hospital site. Each stratum has exactly four GIM clinical teaching teams. In five hospital sites, each of four GIM clinical teaching teams will be randomized to intervention or control group status using numbers generated at random by the web site [28], a website service for generating random numbers. Two clinical teaching teams will be intervention teams; two others will be control teams. Assignment of teams is not performed in 'batch mode.' In other words, each unique hospital site's four teams will be assigned a group status with just a few months' lead time, usually after the conclusion of the intervention period at a previous site.

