#### Length of stay

Mean lengths of stay will be compared between patients discharged from intervention and control group CTTs. Intervention group effects will be estimated with linear mixed models.

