#### Covariates

Model-based estimates of intervention effects on the outcomes of readmission, length of stay, use of optimal drug therapy, patient satisfaction, and use of paging devices will employ patient-level and team-level covariates. Patient-related factors to be controlled will be patients' age and gender.

Other covariates will be measures of hospital health care processes hypothesized to be related either to outcome measures or to intervention uptake. The intervention's focal concern is the improvement of interprofessional performance of GIM teaching teams. Therefore, we propose to use the following constructs as structural indicators of functional team processes of care:

• *Ward-based assignment of medical, nursing, and allied health professional staff*. 'Ward basing' refers to hospital practices specifying the deployment of healthcare staff members to a single physical ward location. This arrangement is in contrast to assignments that have staff members working among different medical teams or nursing units as they treat patients. For example, if nurses and nursing units are fixed to physical ward locations, then medical team and professional health staff members could be assigned to patients in such a way that they are required to work with members of several different nursing units. If so, they are said to 'cross teams or units.' On the other hand, if medical teams are fixed to physical ward locations, then it is possible that nurses and professional health staff could be required to work among multiple different medical teams. It is also possible that both medical teams and nursing units are given fixed assignments to single ward locations and professional health staff are assigned to work across multiple combinations of medical teams and nursing units. All of these configurations create variation in the degree to which GIM staff are consolidated to work in one physical location.

Work assignments that see GIM staff consistently – and as a matter of hospital policy – working in multiple physical locations, where work colleagues are more likely than not to be unfamiliar, might have negative impacts on achievement of effective interprofessional collaboration and patient outcomes. An indicator variable will be developed to code whether clinical teaching teams are organized to consolidate interprofessional teams and team members to a single physical ward location.

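### Randomisation is stratified by hospital, but no stated test, model or covariate list includes hospital; if hospitals differ in outcome, precision is lost

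*Protocol article*

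**What the plan says.** **Design.** Sequence generation states: "Stratification is by hospital site. Each stratum has exactly four GIM clinical teaching teams". Within each site, "Two clinical teaching teams will be intervention teams; two others will be control teams". Sites are assigned one at a time, usually after the previous site's intervention period has ended, so site also carries calendar period.

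**Analysis.** Under Statistical methods, Readmission, the difference in proportions is "tested with chi-square and association statistics adjusted for the cluster randomized design", and GEE is then used for clustering, with clusters identified as teams. For length of stay, "Intervention group effects will be estimated with linear mixed models". The staff survey and paging also get linear mixed models, and satisfaction and drug therapy get GEE. Hospital is named in none of these as a stratum, fixed effect or random effect.

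**Covariates.** Models for every outcome except the staff survey "will employ patient-level and team-level covariates". These are patient age and gender, then ward basing, discharge planner, time in interdisciplinary rounds, nursing staff characteristics and nursing workload. There is no hospital indicator.

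**Sample size.** "We assume an intracluster correlation coefficient of 0.01". It is a single value, not split into hospital and team parts. The section also states: "we expect there will be in excess of 200 patients admitted into each clinical teaching team in the 2-month intervention period". For 10% v 5%: "When significance is set at p < 0.05, the trial would have 93% power". For 5% v 2.5%, the stated power is 67%.

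**The concern.** Because each hospital contributes two teams to each arm, differences between hospitals cancel from the treatment contrast. An analysis that treats the 20 teams as exchangeable still counts those differences as error. Its standard error then exceeds the true sampling variability of the contrast, and the precision that stratification was meant to buy is not collected.

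The protocol gives reasons to expect hospital differences. The Covariates section says that discharge planning is organised differently across sites and suggests that this influences readmission and length of stay. The sequential roll-out adds calendar time to the site effect.

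The omission also sits in a detailed list. The Covariates section goes as far as alternative definitions of nursing mix, yet leaves out the one factor on which the randomisation was built.

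**Working it through.** **Inputs from the protocol:** 5 hospitals, 4 teams each (2 v 2), 200 patients per team, ICC 0.01, readmission 10% v 5% or 5% v 2.5%, alpha 0.05 (sidedness not stated). **Assumed:** the share s of the ICC that lies between hospitals. The protocol does not give it, so 0 to 100% is shown.

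**1. Stated power.** Design effect = 1 + 199 × 0.01 = 2.99. Effective n per arm = 2000/2.99 = 668.9. A two-sided two-proportion test gives 93.6% (stated 93%) and 67.3% (stated 67%), so both reproduce. They use the full ICC and take no credit for stratification.

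**2. Standard errors.** Let b = p1(1−p1) + p2(1−p2).

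- True variance of the difference under the 2 v 2 design, which a model with site estimates: b × [0.99 + 2(1−s)]/2000, where 0.99 = 1 − 0.01 and 2 = 200 × 0.01.
- Variance estimated when site is ignored: b × [0.99 + 2(1−s) + 2s × 8/9]/2000. The factor 8/9 = (10/9)(1 − 1/5) arises because the ten teams in an arm come from five hospitals, two from each.

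SE ratio, ignored to included:

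- s = 25%: √(2.934/2.49) = 1.085
- s = 50%: √(2.879/1.99) = 1.20
- s = 75%: √(2.823/1.49) = 1.38

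Site uses 4 of the 18 team-level df. The t quantile rises from 2.101 to 2.145, which multiplies these ratios by 0.98. The interval-width ratios become about 1.06, 1.18 and 1.35. Setting the width ratio to 1 gives a break-even share of about 7%.

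**3. Simulation** (40,000 runs per setting; team-level t test; site ignored with 18 df v site as fixed effect with 14 df; type I error simulated at 10% in both arms; width ratio from the 10% v 5% setting):

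| Share s | Type I error, ignored v included | Power 10% v 5% | Power 5% v 2.5% | Interval width ratio |
|---|---|---|---|---|
| 0% | 4.7% v 4.7% | 90.7% v 89.7% | 62.1% v 60.6% | 0.98 |
| 25% | 3.7% v 5.1% | 92.6% v 94.2% | 63.4% v 68.0% | 1.07 |
| 50% | 2.4% v 5.1% | 94.5% v 97.7% | 65.7% v 77.2% | 1.18 |
| 75% | 1.4% v 5.1% | 96.1% v 99.4% | 68.7% v 87.4% | 1.34 |
| 100% | 0.5% v 4.8% | 97.1% v 100.0% | 71.4% v 95.7% | 1.61 |

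**4. Uncorrected sandwich.** The protocol names GEE without a small-sample correction. A GEE-like sandwich z test on 20 teams that ignores site has type I error 7.6%, 6.0%, 4.3%, 2.6% and 1.2% at shares of 0, 25, 50, 75 and 100%. It crosses 5% at a share of roughly 40%. At a 50% share its power is 97.1% and 74.9% in the two scenarios, close to the 97.7% and 77.2% of the corrected test with site.

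**The case against.** - **The consequence is conditional.** A reader might infer that the intervals are simply too wide and power is thrown away. The documents do not support that. It needs between-hospital variance, and Sample size gives one undivided ICC. With none between hospitals, ignoring site makes the t interval 2% narrower and gains about 1 power point. This stands.
- **The direction can reverse.** With an uncorrected sandwich variance, the test that ignores site is anti-conservative at low shares (step 4). This stands too, but two errors of unknown size that partly cancel do not justify the analysis.
- **Silence is not exclusion.** The mixed models list no random effects, not even team, and the cluster-adjusted chi-square rests on cited sources that are not at hand. The Intervention section says in general terms that teams' outcomes will be compared at each site. So it cannot be claimed that hospital has been ruled out. Still, that sentence sets no method, and the covariate list is explicit and lacks hospital.
- **Listed covariates may absorb part of the site effect.** Discharge planning differs by site, and ward basing is described as hospital practice. This is true in part, but a few process measures need not span four site contrasts or calendar period.
- **The main scenario hardly suffers.** At shares of 25% and 50%, the loss for 10% v 5% is about 2 and 3 points. This stands; the larger loss is in the 5% v 2.5% scenario.

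**Conclusion.** The stated analysis does not reflect the stratified randomisation. That part rests on the text alone. The cost depends on how much of the ICC lies between hospitals, which the protocol leaves open.

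Under a small-sample t analysis, ignoring site loses precision once roughly 7% or more of the ICC lies between hospitals. At an assumed 50% share it costs about 3 power points for 10% v 5% and about 11 for 5% v 2.5%. If the planned GEE uses an uncorrected sandwich variance, conservatism appears only above roughly a 40% share; below that, the lack of a small-sample correction is the larger problem.

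A reader might also infer that the stated power is wrong. It is not: 93% and 67% reproduce and assume no gain from stratification. The power simulations cover readmission only. For the secondary outcomes the same reasoning applies, but its size is unknown.

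**What to change.** - Include hospital site, as a fixed effect (four indicators) or as a stratum, in the primary GEE and in the GEE and mixed models for the secondary outcomes.
- Use a site-stratified version of the cluster-adjusted chi-square.
- State a small-sample correction for inference based on 20 teams.
- Keep the team-level covariate list short, and drop any covariate that is constant within a hospital, since it is collinear with the site indicators.

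**Cost.** Design and data collection do not change. Site takes 4 of 18 team-level df, about 1 power point if hospitals do not differ. The covariate plan has to be revised: 18 − 4 = 14 df remain, and one term for each of the five listed team-level families would leave 14 − 5 = 9.
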